## Statistical criteria of termination of trial

No statistical criteria are planned.

## Planned Analyses

A detailed description of data preparation and analysis will be elaborated as below:

### Datasets to be analysed, analysis populations

The full analysis set will include all randomised patients. They will be analysed according to the group they were randomised to regardless of the tracer actually used according to the intention-to-treat principle. We will also define a per-protocol analysis set that excludes major protocol violations.

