## Dose Rationale

^68^Ga-PSMA-11 examination protocol

We will apply, in accordance with the “Fachliteratur”, 150 MBq ± 15% of ^68^Ga-PSMA-11.

Ideally, the dose applied would be the same as that of the comparator. As a result of a change in production of ^68^Ga-PSMA-11 from the Unilabor Bern to SWAN Isotopen AG, interruptions and periods of non-production are expected and have been experienced. In these cases, the radiopharmaceutical will be sourced from the Radiopharmazie of the USZ and from EURO-PET-GmbH (Freiburg im Breisgau, Germany). Here the radiopharmaceutical is produced under identical conditions, and both producers hold TLD licences. Higher doses (300 MBq) cannot be guaranteed as a result of the long logistics chain, and in any case, would be outwith the Fachliteratur. We will therefore apply 150 MBq but increase the acquisition time to obtain the same count statistics as if 300 MBq had been applied (this is equivalent to the photography concept of “exposure”). The “Fachliteratur” for ^18^F-PSMA-1007 defines, without any basis in evidence, an acquisition time of 2h; this is not specified in the literature for ^68^Ga-PSMA-11, although later acquisitions are known to lead to increased tumour-to-background ratios [18].

For all patients PET/CT examinations will be performed at 2h (± 10min) post application of the radiotracer as described, with image acquisition from the thighs to the skull base, as per institutional protocol. Before each scan, the patients will be asked to empty their bladder.

As described above, given the urinary excretion of ^68^Ga-PSMA-11 which can obscure lesions contiguous with the bladder, furosemide is given as per routine clinical protocol. 20mg of furosemide will be given intravenously (i.v.) 20-30 min prior to the final scan [19]. 1L of water will be provided to the patients to drink.

^18^F-PSMA-1007 examination protocol

We will inject a dose of 300 MBq ± 15% of ^18^F-PSMA-1007 intravenously with PET/CT examinations 2h post application of radiotracer as described in the “Fachinformation” (Appendix A) for ^18^F-PSMA-1007. PET/CT will be performed from thighs to skull base, as per institutional protocol. No further preparations are necessary due to the limited renal excretion of this tracer. The patient will empty his bladder prior to each scan.

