### Handling of Drop outs

Should a patient withdraw prior to completion of the second examination, that patient will be replaced and recruitment will continue until 100 patients have been recruited.

For patients who withdraw consent at any point, the data up to the time point of withdrawal will be used.

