## Determination of Sample Size

Power was determined using Monte Carlo simulations with 1000 repetitions and the following assumptions:

- Marginal probabilities: 80% of the patients are positive for tracer A and 80% are positive for tracer B
- Both tracers are applied to each patient
- Non-inferiority design with a one-sided alpha of 2.5%
- Non-inferiority margin of -10% (clinically acceptable margin in detection rate, balanced against the requirements for clinically realistic number of patients). We justify this margin as being less than 50% of the margin reported for superiority (22%) in a prospective trial published for ^68^Ga-PSMA-11 versus the first-generation tracer ^18^F-Choline [22].
- Non-inferiority is concluded if the lower limit of a 95% confidence interval (Wald with Bonett–Price Laplace adjustment) for the difference in the proportion of tracer-positive patients (new tracer – old tracer) is larger than the non-inferiority margin
- A pragmatic assumption is made regarding the correlation of the paired measurements. Limited data are available for this, given the dearth of comparative studies. Neither retrospective analyses [28] nor limited pilot studies [17, 27] have demonstrated any difference in detection rate. We take a worst-case scenario, and assume that both tracers are positive for 75% of the patients.

Data was simulated using function rmvbin from R package bindata [29]. With 100 patients we will have a power of 85% to detect non-inferiority.

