### Primary Analysis

The primary outcome (proportion of patients with PSMA-positive pathological lesions) will be compared between tracers using an absolute risk difference (new tracer minus old tracer) with a one-sided lower 95% confidence interval (CI) for paired proportions (Wald with Bonett–Price Laplace adjustment). If the lower limit lies above -10%, we will claim non-inferiority. Proportion of pathologic scans will be based on majority consensus reads.

The number of PSMA-positive lesions defined as pathological, benign and uncertain in each region will be analysed using separate mixed-effects Poisson regression models with tracer as fixed covariate and nested random effects for patient and region. We will report incidence rate ratios with 95% CI and p-values. As a sensitivity analysis we will compare the number over all regions using the Wilcoxon signed-rank tests and the Mann-Whitney statistic with 95% CI.

Inter-reader reliability will be analysed on the region-level based on the number of benign, pathological and uncertain lesions determined by each reader. We will calculate Krippendorff’s alpha with a ratio difference function and bootstrap 95% CI separately for each tracer.

Lesion-based PPV will be calculated for each tracer as the proportion of pathological lesions confirmed pathological during follow-up among all lesions with a known state and will be presented with 95% Wilson score CI. Using all lesions with a confirmed status during follow-up, the two tracers will be compared using McNemar’s test and an absolute risk difference with 95% confidence interval.

The semi-quantitative tumour to background ratio will be summarized on a region-level (i.e. using the mean over all positive lesions per region) and analysed using a linear mixed-effects regression model with tracer as fixed covariate and patient and region as nested random effects. The mean difference with 95% CI will be reported.

For the subset of patients with additional parametric imaging data (N=10) the planned analysis of parametric imaging parameters (see first secondary endpoint) is planned prior to completion of the study. This exploratory analysis of this secondary endpoint will not assess the primary endpoint and will not influence further trial conduct or further trial process.

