### Secondary Analyses

Secondary analyses of all outcomes will be done in the per-protocol analysis set.

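### The analysis-set rule labels scans by assigned sequence instead of by the tracer injected, which in a paired tracer comparison can only shrink a true difference toward non-inferiority

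*Protocol*

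**What the plan says.** Section 11.4.1 of the protocol defines the main set: "The full analysis set will include all randomised patients". It continues: "They will be analysed according to the group they were randomised to regardless of the tracer actually used according to the intention-to-treat principle". A per-protocol set without major violations is also defined, and section 11.4.3 gives it a supporting role: "Secondary analyses of all outcomes will be done in the per-protocol analysis set". By implication the full analysis set carries the primary claim.

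Section 6.2.1 randomises patients to one of two orders: group A has 18F-PSMA-1007 first, group B has 68Ga-PSMA-11 first. Every patient is meant to receive both tracers.

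Section 11.4.2 takes the risk difference, new tracer minus old, "with a one-sided lower 95% confidence interval (CI) for paired proportions (Wald with Bonett–Price Laplace adjustment"), and claims non-inferiority if the lower limit lies above −10%.

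On incomplete patients, section 7.4.2 states: "Should a patient withdraw prior to completion of the second examination, that patient will be replaced". Recruitment then goes on to 100. Sections 7.4.2 and 11.5 keep the data collected up to withdrawal, and section 9.2.5 foresees patients who miss the second scan because of an adverse event.

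**The concern.** Intention-to-treat protects a comparison between randomised groups. This primary comparison is not between groups: each patient is his own control, and the randomised factor is scan order. Analysing by assigned group whatever tracer was given therefore protects nothing. Its only possible effect on a within-patient tracer difference is to attach the wrong tracer label to a scan. In a superiority trial that would be conservative. In a non-inferiority trial it works in favour of the claim, because mislabelling moves a true deficit toward zero.

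The rule also sits badly with section 6.1.2, where one trio of readers reads all scans of one tracer and another trio reads all scans of the other. A result produced by the 18F readers could end up counted as a 68Ga result.

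A second mismatch lies in the denominator. A set of all randomised patients includes those with one scan, a paired interval needs two results, and the drop-out section replaces those same patients. The sections do not agree on who is counted.

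**Working it through.** **Inputs from the protocol (section 11.2).** 100 patients; 80% positive on each tracer; 75% positive on both; "Non-inferiority design with a one-sided alpha of 2.5"%; "Non-inferiority margin of -10% (clinically acceptable margin in detection rate"). The planned discordant cells are 80% − 75% = 5% positive on the new tracer only and 5% on the old tracer only.

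**Interval.** With b new-only and c old-only patients among n, the Bonett–Price form uses p̃₁₀ = (b + 1)/(n + 2), p̃₀₁ = (c + 1)/(n + 2), d = p̃₁₀ − p̃₀₁ and SE = √[(p̃₁₀ + p̃₀₁ − d²)/(n + 2)]. Non-inferiority is claimed if d − z·SE > −0.10. Rejection rates come from exact enumeration over b and c.

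**The plan's own figure.** With cells 5%/5%, n = 100 and z = 1.96, power is 86.5%. The stated 85% came from 1000 simulations (simulation standard error about 1.1 points), so it is reproduced. With z = 1.645, power would be 92.0%, which does not match, so z = 1.96 is used below. That section 11.4.2 calls the limit one-sided 95% is a separate matter.

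**Effect of the labelling rule.** Assume a share s of patients receives the tracers in reverse order, unrelated to their results. Counting by assigned tracer gives

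- new-only: q₁₀ = (1 − s)p₁₀ + s·p₀₁
- old-only: q₀₁ = (1 − s)p₀₁ + s·p₁₀
- difference: q₁₀ − q₀₁ = (1 − 2s)(p₁₀ − p₀₁)

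For example, with p₁₀ = 5%, p₀₁ = 15% and s = 5%: q₁₀ = 5.5%, q₀₁ = 14.5%, difference −9.0 points instead of −10.

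**False non-inferiority at a true −10 points (n = 100, z = 1.96).** The protocol gives neither s nor the discordance under inferiority. The first split keeps the protocol's 5% new-only cell; the second assumes less discordance.

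| Swapped share s | Expected difference | Cells 5%/15% | Cells 2%/12% |
|---|---|---|---|
| 0 | −10.0 | 2.7% | 3.7% |
| 2% | −9.6 | 3.3% | 4.5% |
| 5% | −9.0 | 4.4% | 6.0% |
| 10% | −8.0 | 6.9% | 9.4% |

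The excess over 2.5% in the first row belongs to the interval method. The rule itself adds roughly 2 points at 5% swapped and 4 to 6 points at 10%.

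**Alternatives.** Labelling by tracer received keeps all 100 pairs and leaves the error at the first-row value for any s. Excluding swapped patients gives 2.8% to 2.9% with 90 to 98 pairs (5%/15%). If the tracers are equal, p₁₀ = p₀₁ and swapping changes nothing.

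**One-scan patients.** Using complete pairs only, power under the planning assumptions is 86.5% (100 pairs), 83.9% (95) and 81.0% (90), and the error at 5%/15% stays between 2.7% and 2.9%. They cost power if not replaced; they do not bias the difference by being listed in the set.

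**The case against.** The best defence is that the rule need not relabel anything. A group is a sequence, so a patient can stay in his assigned sequence while each scan keeps its true tracer. Section 11.4.2 compares tracers, readers are tied to a tracer, and section 6.1.1 says a trained reader recognises the tracer at once. In practice a 68Ga scan would probably be read and counted as 68Ga. This lowers the chance of harm. But the primary analysis has no sequence term, so on this reading the clause does nothing, and on its plain reading it mislabels. Neither is a reason to keep it.

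A reader might infer that the protocol expects order swaps, because section 3.5 says that "interruptions and periods of non-production are expected and have been experienced". It does not. The same section answers such breaks by sourcing from other producers, the section on early termination and interruption speaks of an amendment covering the lost time, and section 8.3 allows no change to the scan protocol. Swaps are possible, but no passage announces them.

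A reader might also infer that one-scan patients dilute the difference, or that the interval cannot be computed. Neither holds. Dilution would require imputing such patients as concordant, which no passage proposes, and the interval is computable on complete pairs, which section 7.4.2 replenishes by replacement. How incomplete pairs are handled in detail may properly be left to the analysis plan.

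Finally, a per-protocol analysis of all outcomes is already planned. Making success in both sets mandatory is a trade-off, not a correction of an error.

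**Conclusion.** Wrong as written. The labelling clause does not fit a within-patient tracer comparison, and where it has any effect, that effect shrinks a true deficit and so favours the claim. The direction is certain; the size is not, since it depends on a swap rate that the protocol does not give. Under assumed rates of 2% to 10%, a true difference of −10 points, swaps unrelated to results and z = 1.96, false non-inferiority is 3.3% to 6.9% against 2.7% without swaps (5%/15%), or 4.5% to 9.4% against 3.7% (2%/12%). With no swaps or equal tracers the effect is nil.

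The denominator point is smaller: the inclusion of all randomised patients, the paired interval and the replacement rule should describe the same set. The documents do not support reading it as a source of bias.

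**What to change.** In section 11.4.1, strike the clause that ignores the tracer given and state that each scan is classified by the tracer actually injected. Define the primary set as randomised patients with both scans evaluable, and bring section 7.4.2 into line with it. Report the numbers of one-scan patients and of order deviations, with a sensitivity analysis for them. Show the already planned per-protocol result beside the primary one as a consistency check.

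The cost is minor amendment wording and one added sensitivity analysis. No extra patients or scans are needed.

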### Primary Analysis

The primary outcome (proportion of patients with PSMA-positive pathological lesions) will be compared between tracers using an absolute risk difference (new tracer minus old tracer) with a one-sided lower 95% confidence interval (CI) for paired proportions (Wald with Bonett–Price Laplace adjustment). If the lower limit lies above -10%, we will claim non-inferiority. Proportion of pathologic scans will be based on majority consensus reads.

The number of PSMA-positive lesions defined as pathological, benign and uncertain in each region will be analysed using separate mixed-effects Poisson regression models with tracer as fixed covariate and nested random effects for patient and region. We will report incidence rate ratios with 95% CI and p-values. As a sensitivity analysis we will compare the number over all regions using the Wilcoxon signed-rank tests and the Mann-Whitney statistic with 95% CI.

Inter-reader reliability will be analysed on the region-level based on the number of benign, pathological and uncertain lesions determined by each reader. We will calculate Krippendorff’s alpha with a ratio difference function and bootstrap 95% CI separately for each tracer.

Lesion-based PPV will be calculated for each tracer as the proportion of pathological lesions confirmed pathological during follow-up among all lesions with a known state and will be presented with 95% Wilson score CI. Using all lesions with a confirmed status during follow-up, the two tracers will be compared using McNemar’s test and an absolute risk difference with 95% confidence interval.

The semi-quantitative tumour to background ratio will be summarized on a region-level (i.e. using the mean over all positive lesions per region) and analysed using a linear mixed-effects regression model with tracer as fixed covariate and patient and region as nested random effects. The mean difference with 95% CI will be reported.

For the subset of patients with additional parametric imaging data (N=10) the planned analysis of parametric imaging parameters (see first secondary endpoint) is planned prior to completion of the study. This exploratory analysis of this secondary endpoint will not assess the primary endpoint and will not influence further trial conduct or further trial process.

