| **Number of Participants with Rationale:** | Recruitment will be open until 100 patients have been recruited.  Assuming that 80% of the patients are positive for each one of the tracers and that 75% of the patients will be positive for both tracers, recruitment of 100 patients will give a power of 85% to detect non-inferiority with a non-inferiority margin of -10% and a one-sided alpha of 2.5% using the Wald confidence interval for paired proportions with the Wald Bonett-Price Laplace adjustment. |
| **Study Duration:** | 2 years |
| **Study Schedule:** | First patient examination: June (planned) 2022*  Last patient examination: June 2023*  Follow-up of 6 months (until end of Dec 23)*  Data analysis and publication within 6 months (until June 2024)*  * See additional text in Section “Study Schedule” |
| **Investigator(s):** | Sponsor: [name]. med. [name]  Principal Investigator: [name]. med. [name]  Klinik für Nuklearmedizin, Inselspital Bern  [name]  [name]  [contact]  [contact] |
| **Study Centre(s):** | Single-centre (University Clinic for Nuclear Medicine, Inselspital Bern) |

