| **Statistical Considerations:** | **Primary Endpoint:**  The primary outcome (proportion of patients with PSMA-positive pathological lesions = patient based sensitivity) will be compared between tracers using an absolute risk difference (new tracer minus old tracer) with a one-sided lower 95% confidence interval for paired proportions (Wald with Bonett–Price Laplace adjustment). If the lower limit lies above -10%, we will claim non-inferiority. Detection rates per patient will be based on majority consensus reads.  **Secondary Endpoints:**   - Parametric imaging will be performed for the two radiotracers in a subset of patients (n=10*), allowing comparison of the tracers’ dosimetric and kinetic parameters, with affinity for the PSMA radioligand by calculation of the parametric equilibrium constant *K*_D,_ which will be compared between the two tracers with descriptive statistics. - The number of PSMA-positive lesions defined as pathological, benign and uncertain per region will be compared using mixed-effects Poisson regression. Patient-level data will also be analysed using the Wilcoxon signed-rank test.. - Inter-reader reliability will be compared on the region level using Krippendorff’s alpha for benign, pathological and uncertain lesions, separately for the two tracers. - Region based PPV will be calculated for each tracer separately with 95% Wilson score confidence intervals. The two tracers will be compared using McNemar’s test and an absolute risk difference with 95% confidence interval. - Semi-quantitative tumour to background ratio (defined as lesion SUV ÷ SUV of reference background region, where the background uptake is defined by convention as the left gluteal musculature) will be summarised on a region-level (i.e. using the mean over all positive lesions per region). Summarised data will be analysed using linear mixed-effects regression models. - The number and severity of adverse event will be analysed using descriptive statistics. All serious adverse events will be listed.   *The requirement for N=10 patients is justified on the previous dosimetry paper for the established PET radiotracer ^68^Ga-PSMA-11 which was adequately powered to demonstrate a mean-effective dose of 0.023 ± 0.004 mSv/MBq, i.e. with a precision in the µSv range [1]. |

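### The primary non-inferiority test is sized at one-sided 2.5%, but the analysis section, read literally, tests at one-sided 5%

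*Protocol*

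**What the plan says.** **Sizing.** Protocol section 11.2 (Determination of Sample Size) lists "Non-inferiority design with a one-sided alpha of 2.5" per cent among its assumptions. It gives the rule as "Non-inferiority is concluded if the lower limit of a 95% confidence interval" (Wald with the Bonett–Price adjustment) lies above the margin. It does not call that interval one-sided. At an alpha of 2.5% it is the lower end of a two-sided 95% interval. The synopsis row on number of participants repeats "a non-inferiority margin of -10% and a one-sided alpha of 2.5" per cent. Both places state 85% power with 100 patients.

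**Analysis.** Section 11.4.2 (Primary Analysis) makes the comparison "using an absolute risk difference (new tracer minus old tracer) with a one-sided lower 95% confidence interval (CI) for paired proportions", and then: "If the lower limit lies above -10%, we will claim non-inferiority". The synopsis row on statistical considerations also works "with a one-sided lower 95% confidence interval for paired proportions". Neither place names an alpha.

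The margin, the effect measure and the interval method are the same throughout. Only the confidence level differs, and nothing in the protocol reconciles the two.

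**The concern.** A one-sided 95% lower limit lies 1.645 standard errors below the estimate and corresponds to a one-sided 5% test. A one-sided alpha of 2.5% needs 1.960 standard errors. Both cannot be the primary rule.

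This is the success criterion for the primary objective. If the result falls between the two limits, the trial is non-inferior by section 11.4.2 and not by section 11.2, and the choice would have to be made with the data in view. The error also runs in the lenient direction. The section that governs the analysis is the one that makes it easier to accept a tracer whose positivity rate is 10 points lower.

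**Working it through.** **Inputs (section 11.2 unless noted)**
- n = 100 patients, each scanned with both tracers.
- Marginal rates: "80% of the patients are positive for tracer A and 80% are positive for tracer B".
- Both tracers positive in 75%. The discordant cells are therefore 80% - 75% = 5% new-only and 5% old-only, with a true difference of 0.
- Margin -10%.
- Stated power 85%, from 1000 simulated trials. Its Monte Carlo standard error is √(0.85 × 0.15 / 1000) = 1.1 points.
- z = 1.960 for one-sided 2.5% (section 11.2) and z = 1.645 for one-sided 5% (section 11.4.2 read literally).

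**Formula.** With x new-only and y old-only positive patients, the Bonett–Price limit uses
- p₁ = (x + 1)/(n + 2) and p₂ = (y + 1)/(n + 2)
- d = p₁ - p₂
- SE = √[(p₁ + p₂ - d²)/(n + 2)]
- lower limit = d - z × SE, with non-inferiority claimed if it exceeds -0.10.

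Power and error are obtained by summing the exact trinomial probabilities of all (x, y) that meet the criterion.

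**Step 1: reproduce the stated power (cells 5% / 5%)**

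| Rule | Exact power | Compared with the stated 85% |
| --- | --- | --- |
| z = 1.960 (one-sided 2.5%) | 86.5% | 1.5 points, about 1.3 Monte Carlo standard errors |
| z = 1.645 (one-sided 5%) | 92.0% | 7.0 points, about 6 Monte Carlo standard errors |

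The sample size was computed at one-sided 2.5%. Under the 5% rule, about 78 to 84 patients would already give 85%.

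**Step 2: error rate at the margin (true difference -10 points).** The protocol gives no discordance for this case, so the new-only rate is an assumption and is varied. The old-only rate is 10 points higher.

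| New-only / old-only | z = 1.960 | z = 1.645 | Ratio |
| --- | --- | --- | --- |
| 1% / 11% | 4.2% | 6.2% | 1.5 |
| 2% / 12% | 3.7% | 6.0% | 1.6 |
| 5% / 15% | 2.7% | 5.7% | 2.1 |
| 10% / 20% | 2.5% | 5.3% | 2.1 |

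The nominal level doubles exactly, from 2.5% to 5%. The attained error rises by a factor of about 1.5 to 2.1.

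**Step 3: a data set on which the sections disagree.** Take x = 5 and y = 8.
- p₁ = 6/102 = 0.0588 and p₂ = 9/102 = 0.0882, so d = -0.0294
- SE = √[(0.1471 - 0.0009)/102] = 0.0379
- z = 1.960: lower limit -10.4%, non-inferiority not shown
- z = 1.645: lower limit -9.2%, non-inferior

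The same happens with x = 3 and y = 7 (-10.5% and -9.5%).

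**Step 4: how often this would happen.** Every trial that passes at z = 1.960 also passes at z = 1.645. Under the planning assumptions the two rules therefore disagree in 92.0% - 86.5% = 5.5% of trials.

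**The case against.** The strongest reply is that there is only one intended test and the analysis text names it clumsily. Alpha appears in two places and is one-sided 2.5% in both. Section 11.2 also states a decision rule, with the same interval method, that is consistent with that alpha. The stated power reproduces only at 2.5%. On this reading, the one-sided lower 95% interval means the lower end of an ordinary two-sided 95% interval, and the planned error rate has not moved.

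That is probably how the wording arose, and it shows which rule should be kept. It does not remove the contradiction. The phrase has a definite meaning, appears twice, and one of the two places is the section an analyst would follow.

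Two further limits are fair. The attained error does not double in every scenario, as Step 2 shows. The rules also disagree in only about one trial in eighteen under the planning assumptions, and the examples above were picked from that band.

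A statistical analysis plan, not shown here, could name the bound explicitly. It would then depart from one of the protocol's two statements, and the protocol would still contradict itself.

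**Conclusion.** The point holds and should be corrected before the primary analysis. The protocol sizes its primary test at one-sided 2.5% and, read literally, analyses it at one-sided 5%. The sample size calculation is sound; the fault is in the wording of section 11.4.2 and the synopsis statistics row.

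The power figures rest on the protocol's own assumptions (80% positive on each tracer, 75% on both, 100 patients with complete pairs). The error rates at the margin rest on assumed new-only rates of 1% to 10%. The doubling of the nominal level rests on no assumption beyond the literal reading of the text.

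**What to change.** In section 11.4.2 and in the synopsis row on statistical considerations, replace the one-sided lower 95% interval with the lower limit of the two-sided 95% confidence interval for paired proportions (Bonett–Price), and add that this is a one-sided 97.5% limit, alpha 2.5%. In section 11.2, insert the word two-sided before the 95% interval so that all four places read alike.

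The cost is an amendment with these wording changes, made before the reads are unblinded for analysis. The criterion becomes stricter than section 11.4.2 now reads. The 100 patients and the stated 85% power stay as they are, because they were already computed under this rule.
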